**Trial flow chart.**

#### Inclusion criteria

Should be a registered case of new pulmonary TB, either sputum smear positive or negative ( *new TB patients are defined as those who have no history of prior TB treatment or who received less than 1 month of anti-TB drugs, regardless of whether their smear or culture results are positive or not).*Should be a non-smoker.Have not taken part in a 'Smoke Free Homes’ activity before.Residing within the same district.Aged more than 10 years.Lives with at least one other person who smokes tobacco on a regular basis without any restrictions in the house.

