#### Patient randomisation

The research team will draw simple randomisation tables where the unit of randomisation will be individuals. The 150 cases will be randomised in to two arms with 75 cases in each arm. The record of randomisation codes and allocation will be maintained by the principal investigator. Once randomised, a participant cannot be withdrawn from the trial. The RA will remain blinded to the fact regarding which arm has been allocated to the patient and will deliver the individual based care to all patients registered in the trial. Once a patient will be registered the information will be send by the RA to the principal investigator who will allocate the arm and inform the co-investigator. The SMS or letter to the arm 2 registered patients will be send by the researcher away from the TB centre. The trial register will be kept in researcher office under lock and key and only the principal investigator will have access to it.

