#### Outcome assessments

All outcomes will be measured after the intervention in each of the study’s arms. The *Primary outcome* will be SFH of non-smoker TB patient by validating through 'Urine Cotinine’ test. During the trial process two urine samples will be collected for cotinine testing at time of registration '0 month’ and at completion of '2 month’ of treatment. The first test will establish the base line where as the test at 2 month will be used to validate the effect of intervention. The urine cotinine testing will be done by the laboratory technician in the TB clinic who will receive relevant training on the conduct of the test and its interpretation. The RA will be kept blinded to the results of urine cotinine and the results will be collected by the researchers directly from the laboratory.

The *Secondary outcomes* will be mainly patient cure rates. All type of patient treatment outcome will be documented including; cured, completed, default, died, failure and transfer out.

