#### Data analysis

Summaries of the baseline characteristics of participants will be presented by trial arm, and recruitment and attrition rates will be reported. Although it is a pilot trial and the ample size has not been powered to estimate the likely effect size of the primary outcome, a comparison between the two intervention arms will be undertaken to determine the difference in the outcome between two arms adjusting for health centre. Differences of the secondary outcome between the two arms will also be reported. Analyses will be conducted under the principle of intention to treat, with individual participant as the primary unit of analysis.

### Objective 3

To determine the barriers and key drivers to the creation of smoke free homes. (Phase III).

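### Cure rate is a poor headline secondary outcome for a trial that enrols smear-negative patients: participants who complete treatment without being classed as cured count as not cured

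*Protocol article*

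**What the plan says.** Under Outcome assessments, the protocol article states that the secondary outcomes "will be mainly patient cure rates". It then lists the treatment outcomes to be documented: "cured, completed, default, died, failure and transfer out". Cured and completed are thus distinct results for a patient. Neither is defined, and no denominator for the cure rate is given.

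Under Inclusion criteria, a participant must be a "registered case of new pulmonary TB, either sputum smear positive or negative".

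Under Patient randomisation, the article says "The research team will draw simple randomisation tables where the unit of randomisation will be individuals", with 75 cases in each arm. No stratification by smear status is mentioned.

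Under Data analysis, the primary comparison is made "to determine the difference in the outcome between two arms adjusting for health centre". Differences between arms in the secondary outcome will also be reported, and analyses follow intention to treat. Smear status is not mentioned there.

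**The concern.** If cured and completed are separate categories, finishing treatment is not enough to be cured; something more is required. The only TB laboratory test that the Setting section names at these centres is sputum smear microscopy. A patient whose smear was negative at entry has no positive smear to convert, so completed is plausibly that patient's best attainable result. A headline outcome of cure would then score some good outcomes as failures, in the same column as default, death and treatment failure.

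Two things are at stake. First, the level of the cure rate would depend on the local mix of smear-positive and smear-negative patients, so it would not carry over to a centre with a different mix. Second, any effect on treatment outcome would be harder to see, because part of the sample could not contribute to it.

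**Working it through.** The article gives no expected cure rate, smear mix, significance level, power or effect size for this outcome, so there is no figure of its own to reproduce. Only the 75 per arm comes from the article. The other inputs are assumptions, shown as ranges.

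**Inputs**
- n = 75 per arm (Patient randomisation)
- p = smear-positive share, assumed
- c = probability that a smear-positive patient is classed as cured, assumed
- c0 = probability that a smear-negative patient is classed as cured, assumed 0 at first and then varied

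**Level.** Overall cure rate q = p × c + (1 − p) × c0. With c0 = 0, q = p × c, which cannot exceed p.
- 60% smear-negative: ceiling 40%; with c = 0.75, q = 0.40 × 0.75 = 30%.
- 30% smear-negative: ceiling 70%; with c = 0.85, q = 0.70 × 0.85 = 59.5%.

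So 40-70% is the ceiling and 30-60% is the rate expected at these assumed cure probabilities.

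**Dilution.** Let cure among smear-positive patients rise from 0.80 to 0.90, and let g0 be the gain in cure among smear-negative patients. The all-patient gain is p × 10 + (1 − p) × g0 points. With g0 = 0 (two-sided 5% level, power for illustration only):

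| p | Gain in cure, all randomised | Power | Gain in cure, smear-positive only | Power |
|---|---|---|---|---|
| 0.3 | 3 points | 6% | 10 points | 15% |
| 0.5 | 5 points | 9% | 10 points | 22% |
| 0.7 | 7 points | 14% | 10 points | 30% |

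Cured plus completed over all randomised, at 0.80 versus 0.90, has 40% power. That figure assumes that smear-negative patients gain the same 10 points in treatment success; if they gain nothing, success is diluted too. If smear-negative patients can be classed as cured and share in the gain, dilution of cure shrinks: at p = 0.5 and g0 = 5, the all-patient gain is 5 + 2.5 = 7.5 points.

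**Chance variation.** The share of the chance variance of the between-arm cure difference that comes from smear mix is (c − c0)² × p(1 − p) / [q(1 − q)]. With c0 = 0 it runs from 41% (p = 0.7, c = 0.7) to 86% (p = 0.3, c = 0.9). At p = 0.5 and c = 0.8 it depends strongly on c0:

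| c0 | Share from smear mix |
|---|---|
| 0 | 67% |
| 0.2 | 36% |
| 0.4 | 17% |
| 0.6 | 5% |
| 0.8 | 0% |

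This variation is already part of the ordinary binomial variation. With c0 = 0, a smear imbalance at its 95% limit shifts the cure difference by 1.96 × c × √(2p(1 − p)/75). That is 0.110 at p = 0.7, c = 0.75 and 0.136 at p = 0.5, c = 0.85, or 11-14 points. The 95% limit of the whole cure difference is 1.96 × √(2q(1 − q)/75), about 15-16 points for q between 0.30 and 0.60. A standard confidence interval covers the smear component.

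**The case against.** The strongest objection is that the decisive premise is missing from the article. It does not say that smear-negative patients cannot be classed as cured, and the last table shows how much rests on that. This stands: the figures are conditional. What does not depend on the premise is that cured and completed are separate categories, so a patient in the second is not counted in the first.

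A reader might infer that the between-arm cure difference mostly measures smear imbalance and could produce a false arm effect. The article does not support that. Randomisation makes the expected smear difference zero, and the chance component lies inside the usual interval.

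A reader might also infer that this cure rate will be used to size the definitive trial. It is not named for that. The Design section says the definitive trial will assess reduction in second-hand smoke exposure. Under Objective 4, the sample-size inputs named are recruitment and attrition. The pilot's own research question is whether TB treatment outcomes can feasibly be measured, and the trial is stated not to be powered.

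Finally, definitions and denominators may be set out in a fuller document, and since every category is documented, cured plus completed can be derived anyway. Both are fair. The absence of a definition is therefore not the complaint. The complaint is the choice that the article does state: cure as the main secondary outcome in a mixed-smear population.

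**Conclusion.** The point holds as a badly chosen summary measure. Cure, kept apart from completed, is a poor main secondary outcome when smear-negative patients are eligible. On the assumption that smear-negative patients are rarely or never classed as cured, the all-patient rate has a ceiling of 40-70% (30-60% smear-negative), and a 10-point gain among smear-positive patients shows as 3-7 points (smear-positive share 30-70%). The harm is dilution, chance variation and a rate that depends on case mix. It is not systematic bias, and it lessens to the extent that smear-negative patients can be classed as cured. It does not touch the primary outcome. It is worth changing because a more suitable summary can be built from categories already being recorded.

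**What to change.** Make treatment success (cured plus completed) among all randomised participants the main secondary outcome. Report cure only among participants who were smear-positive at registration. Give both by arm with 95% confidence intervals, and add baseline smear status to the table of baseline characteristics by arm. State the programme's definition of cured alongside.

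The Trial status section places data entry and cleaning after the six-month follow-up, so this can be settled before the outcome data are examined. No new outcome category is needed.

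There are two costs. The smear-positive subset is smaller: at a 40-70% share it has about 30-52 patients per arm, and at 80% cure the 95% limit of the difference is 1.96 × √(2 × 0.8 × 0.2/m), with m patients per arm, or about 20 to 15 points. The corresponding limit for success at 80% among all 75 per arm is about 13 points. In addition, smear status must be taken from the centres' records; the Recruitment section cites the TB register only for case type, residence and age, so its availability there should be confirmed.

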#### Data monitoring

Data will be monitored for quality and completeness by the principal and co-investigator using verification, validation and checking processes. Missing data will be pursued until study end unless they are data obtained by participant contact and this would cause distress.

#### Data analysis

Summaries of the baseline characteristics of participants will be presented by trial arm, and recruitment and attrition rates will be reported. Although it is a pilot trial and the ample size has not been powered to estimate the likely effect size of the primary outcome, a comparison between the two intervention arms will be undertaken to determine the difference in the outcome between two arms adjusting for health centre. Differences of the secondary outcome between the two arms will also be reported. Analyses will be conducted under the principle of intention to treat, with individual participant as the primary unit of analysis.

### Objective 3

To determine the barriers and key drivers to the creation of smoke free homes. (Phase III).

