#### Research questions

This pilot trial has been designed to answer the following research questions;
What behaviour change techniques are relevant and appropriate to be used in the development of 'Smoke Free Homes’ intervention?What is the feasibility and fidelity of implementing 'Smoke Free Homes’ intervention in TB patients?What is the proportion of non-smoker TB patients among all registered TB cases and what is the smoking behaviour of residents in their homes?What is the rate and reasons of refusal to participate in the research by the non-smokers with smoker in home?What are the recruitment and attrition rates for participants?What is the likely effect size in relation to the primary outcome measure i.e. reduction in the exposure to second-hand smoke validated by a urinary cotinine test after 2 months of TB treatment?What is the feasibility and acceptability of measuring the primary outcome?What are the barriers of change reported by the TB patient during follow-up?What is the feasibility of measuring TB treatment outcomes among trial participants?

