#### Hypothesis

We hypothesis that the SFH educational materials with or without supplementary support (mobile phone text message 'SMS’ or letter to smoker(s) at home on weekly basis) will be effective in relative or absolute reduction of exposure to tobacco smoke at home in non-smoking TB patients living with smoker(s). The option of supplementary support of SMS or letter seems more powerful as this may persuade the smoker at home in implementing smoking restriction in home.

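### The stated between-arm comparison adjusts for health centre but does not include baseline urine cotinine; adding it would be a cheap efficiency gain whose size depends on the unstated cotinine scale

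*Protocol article*

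**What the plan says.** For the pilot trial, the Data analysis section states that "a comparison between the two intervention arms will be undertaken to determine the difference in the outcome between two arms adjusting for health centre". It names no other covariate, and it says openly that the sample size was not powered for this outcome.

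The Outcome assessments section plans that "two urine samples will be collected for cotinine testing at time of registration '0 month’ and at completion of '2 month’ of treatment", and gives the two tests their roles: "The first test will establish the base line where as the test at 2 month will be used to validate the effect of intervention". No section places the registration value in the between-arm model.

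The form of the outcome varies between sections. In Outcome assessments the primary outcome "will be SFH of non-smoker TB patient by validating through 'Urine Cotinine’ test", which reads as a status. In Research questions the outcome is a "reduction in the exposure to second-hand smoke validated by a urinary cotinine test after 2 months of TB treatment", which could mean a change from baseline. The Hypothesis section also speaks of a reduction, either relative or absolute. No section says whether cotinine is analysed as a level, a change or a positive/negative result.

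**The concern.** A pre-randomisation measurement of the outcome is a natural covariate for a randomised comparison, and this trial already plans to collect it. The stated comparison names centre and leaves that measurement out.

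Precision matters here even though the trial is an unpowered pilot. The Research questions section asks for the likely effect size on the cotinine outcome, and Objective 4 says that the definitive trial's sample size will draw on the pilot. A wider interval than necessary makes the pilot less informative for that purpose.

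The randomisation section describes simple randomisation of individuals and mentions no stratification by baseline exposure. Baseline differences between arms are therefore left to chance, and a model with centre alone does not use what is known about them.

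**Working it through.** **Inputs from the protocol.** Patient randomisation: "The 150 cases will be randomised in to two arms with 75 cases in each arm", so n = 75 per arm (75 + 75 = 150, which agrees). Cotinine is planned at 0 and 2 months. The protocol gives no SD, effect size, power or correlation, so there is no figure of its own to reproduce beyond this sum.

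**Assumption.** The within-arm correlation r between baseline and 2-month cotinine is taken as 0.3, 0.5 or 0.7, with equal variances at the two times. Precision is expressed relative to a comparison of 2-month values that does not use the baseline.

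**Quantitative outcome.**
- Analysis of covariance (ANCOVA): variance factor 1 − r²; SE ratio is its square root; equivalent total sample size is 150/(1 − r²).
- Simple change score: variance factor 2(1 − r); SE ratio is its square root.

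| r | ANCOVA variance | ANCOVA SE ratio | Equivalent total N | Change-score variance | Change-score SE ratio |
|---|---|---|---|---|---|
| 0.3 | 1 − 0.09 = 0.91 | 0.954 | 150/0.91 ≈ 165 | 2 × 0.7 = 1.40 | 1.183 |
| 0.5 | 1 − 0.25 = 0.75 | 0.866 | 150/0.75 = 200 | 2 × 0.5 = 1.00 | 1.000 |
| 0.7 | 1 − 0.49 = 0.51 | 0.714 | 150/0.51 ≈ 294 | 2 × 0.3 = 0.60 | 0.775 |

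ANCOVA therefore cuts the variance by 9%, 25% and 49%. The change score is less precise than ANCOVA in every row. It equals the follow-up-only comparison at r = 0.5 and is worse below that.

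**Chance imbalance.** The SE of the baseline difference between arms is √(2/75) = 0.163 SD. The 95% range is ±1.96 × 0.163 = ±0.32 SD. An imbalance of 0.32 SD would move an unadjusted 2-month contrast by r × 0.32, or about 0.10, 0.16 and 0.22 SD at the three correlations.

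**Binary outcome.** This was simulated from a latent bivariate normal distribution with 75 per arm, assumed outcome proportions of 40% and 60%, a linear model with arm and centre, and 4,000 replicates. The SE ratio compares the model with baseline to the model without it.

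| r (latent) | Quantitative baseline added | Positive/negative baseline added, 95% positive |
|---|---|---|
| 0.3 | 0.976 | 1.001 |
| 0.5 | 0.925 | 0.985 |
| 0.7 | 0.847 | 0.979 |

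The 95% figure is an assumption, but Inclusion criteria make a high proportion plausible, because every participant must live with a regular smoker whose smoking in the house is unrestricted.

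**The case against.** The strongest reply is that this is one condensed sentence in a journal article. It does not say that centre is the sole covariate, and a fuller document may list others. That is a fair limit on how hard the point can be pressed. Still, the section does make a choice: it names one adjustment and passes over the measurement most directly tied to the outcome. Proposing a better stated model is different from complaining of missing detail.

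Several stronger readings are tempting, and the protocol does not support them.

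- *The plan ignores the baseline.* Research questions and Hypothesis speak of a reduction, so the baseline may enter through a change score. What remains is that a change score is the less efficient use of it.
- *The unadjusted comparison is biased by chance imbalance.* Under randomisation this is random error, which the confidence interval already covers. Adjustment removes the part predictable from the imbalance seen; it does not correct a bias.
- *The gain has a known size, such as 150 patients counting as 200.* That needs a quantitative outcome and a correlation that the protocol does not give. Outcome assessments can be read as a binary status, and for the qualitative phase under Objective 3 patients are grouped as successful, partially successful or unsuccessful. With a positive/negative result and almost uniform baselines the gain nearly vanishes.
- *The residual SD for the definitive trial would be lost.* If cotinine is quantitative, it can be computed later from the two planned measurements.
- *Adjustment is free.* It is cheap, but it has the costs set out with the fix.

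**Conclusion.** The point holds as a modest efficiency improvement. No stated figure is wrong and the comparison as written is valid. On a quantitative scale, adding baseline cotinine would reduce the variance of the arm contrast by roughly 9% to 49% for assumed correlations of 0.3 to 0.7, and it would improve on a change score across that range. For a binary outcome the gain is smaller: SE ratios of about 0.98 to 0.85 if a quantitative baseline is available, and close to 1 if the baseline is only positive/negative and almost all are positive. The omission from the stated model is plain in the text. The size of the benefit is uncertain, because it rests on the assumed correlation, on equal variances at the two times and on a cotinine scale that the protocol leaves open.

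**What to change.** First, state the scale on which urine cotinine is analysed.

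- If it is quantitative, compare arms on 2-month cotinine (log-transformed if appropriate) by ANCOVA with terms for arm, health centre and baseline cotinine on the same scale. Report the residual SD and the baseline-to-follow-up correlation, so that the definitive trial can be planned from them.
- If it is binary, adjust for health centre and for the baseline cotinine value where a quantitative one exists. Expect little from a positive/negative baseline if nearly all are positive.

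The cost is a sentence or two in the analysis section, one degree of freedom, and a rule for any missing baselines, since collection from everyone is planned but not assured. If a logistic model is used, the odds ratio becomes conditional on baseline, usually with a larger SE on that scale, and should be described as such. No new data are needed. Trial status places data entry and cleaning after follow-up ends in November to December 2013, so the change could be settled before analysis.

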#### Key activities

We will require an in-depth understanding of the way the intervention has worked within the household setting. This implies the knowledge to be gained from the patients on actual drivers and barriers to effectively impose smoking restrictions in the home. We would be interested in understanding in which ways the patient felt supported in their efforts to keep their home free of smoke, which aspect of the SFH materials were most helpful, which factors motivated the smokers at home to change their behaviour, and which were their main constraints. Since this phase will be post intervention, it would be preferable to use semi structured interviews with key informants to gain this understanding.

#### Participants

The participants will be those from which we have received follow-up urine cotinine result i.e. at the end of 2 months of treatment. There will be 12 participants, six from each arm and representing both hospitals and will be grouped as;
Patients who were successful in imposing smoking restriction in their homes.Patients who were unsuccessful in imposing smoking restriction in their homes.Patients who were partially successful in imposing smoking restriction in their homes.

#### Data collection

We will use an interview checklist and all communications will be tape-recorded and transcribed.

#### Data analysis

The data will be categorized for thematic analysis.

#### Outputs

The understanding gained from this activity will be used to further refine the intervention of SFH individual based care and supplementary support to take account of barriers and enablers to administer smoking restrictions in homes. Moreover, the findings will be also helpful in designing the definitive trial.

### Objective 4

To develop and submit a proposal on a definitive trial based on the pilot trial findings. (Phase IV).

